## MAIN ANALYSES

The main analyses will include the primary and secondary outcomes for registered patients eligible to receive the study drug undergoing THA or TKA for a diagnosis of OA (population 1). In addition, the primary and secondary outcomes will be analysed for populations 2, 3 and 4. Mortality will also be analysed for population 5 (see “Additional analyses” below).

For the primary outcome, the analysis will test the between-group difference of cases developing a symptomatic VTE within 90 days for non-inferiority of aspirin at a margin of 1%. Cluster summary methods will be used to estimate the treatment effect using cluster level differences. These have been shown to be appropriate for cluster-randomised crossover trials with rare outcomes, and the intracluster and interperiod correlation coefficients expected in this trial. The crossover difference per cluster is the mean outcome for the intervention period minus the mean outcome for the control period. In a linear regression of cluster differences on treatment sequence, the treatment effect estimate is the intercept. To account for potential unequal cluster sizes, a cluster size weighted estimator will be used with harmonic mean weights of the number of patients in the two periods, which was the same method used in the interim analyses for incomplete crossover [25, 26]. Treatment effects will be presented as absolute risk differences and 95% confidence intervals will be examined to determine whether the non-inferiority margin has been met and whether superiority of one drug can be concluded. The primary outcome will be presented in Table 3 and Figure 4 will be used to demonstrate whether the non-inferiority margin has been met for the population 1 [30].

The secondary outcomes will investigate non-VTE complications (death, re-operation, readmission and major bleeding events) within 90 days, and reoperation and patient-related pain and function at 6 months (OHS, OKS, EQ-5D and EQ-VAS). Cluster summary methods will be used within an intention-to treat approach. For binary outcomes, the cluster mean per period will be the proportion of patients who had the outcome, while for continuous outcomes such as pain score, the cluster mean will be the mean outcome. Treatment effects will be presented as absolute risk differences and 95% confidence intervals to determine if one treatment is superior to the alternative. Results for the secondary outcomes in population 1 will be presented in tabular form (Table 3) and results for the primary and secondary outcomes in populations 2, 3 and 4 in Table 4.

Due to the early stopping of the trial, final analyses of the primary and secondary outcomes will use the same composite method as the interim analyses which accounts for clusters with incomplete as well as no crossover, with 95% confidence intervals. No bias is expected from early stopping if the patients included in the trial are not systematically different from later patients who would have been included after the trial was stopped. Our composite analysis method accounts for clusters which either had incomplete crossover and or did not crossover. However, the lower sample size and unequal cluster sizes decreases the precision of the outcome estimates. Since we used cluster weighted estimates to account for unequal cluster sizes and increased the initial sample size by 27% above the minimum required, the loss of precision will be mitigated. The trial was stopped based on the Haybittle-Peto

boundary of 0.001, so we anticipate the final analysis using 95% confidence intervals will have sufficient power.

**Table 3.** Outcomes for population 1

| Outcome                                            | LMWH Allocation
(n = X) | Aspirin Allocation
(n = X) | Absolute Risk Difference | 95% Confidence Interval | p-value |
|----------------------------------------------------|----------------------------|-------------------------------|--------------------------|-------------------------|---------|
| Any Venous thromboembolism                  | n (%)                      | n (%)                         | X                        | X – X                   |         |
| Type of Venous thromboembolism              |                            |                               |                          |                         |         |
| Pulmonary embolism                                 | n (%)                      | n (%)                         | X                        | X – X                   |         |
| Deep venous thrombosis                             | n (%)                      | n (%)                         | X                        | X – X                   |         |
| Both Pulmonary embolism and deep venous thrombosis | n (%)                      | n (%)                         | X                        | X – X                   |         |
| Above knee deep venous thrombosis                  | n (%)                      | n (%)                         | X                        | X – X                   |         |
| Below knee deep venous thrombosis                  | n (%)                      | n (%)                         | X                        | X – X                   |         |
| Death                                              | n (%)                      | n (%)                         | X                        | X – X                   |         |
| Re-operation (90d)                                 | n (%)                      | n (%)                         | X                        | X – X                   |         |
| Reoperation (6 months)                             | n (%)                      | n (%)                         | X                        | X – X                   |         |
| Re-admission                                       | n (%)                      | n (%)                         | X                        | X – X                   |         |
| Major Bleeding                                     | n (%)                      | n (%)                         | X                        | X – X                   |         |
| Pain and Function (median and IQR) †    |                            |                               | X                        | X – X                   |         |
| Oxford Hip Score                                   | X (X – X)                  | X (X – X)                     | X                        | X – X                   |         |
| Oxford Knee Score                                  | X (X – X)                  | X (X – X)                     | X                        | X – X                   |         |
| EQ-5D                                              | X (X – X)                  | X (X – X)                     | X                        | X – X                   |         |
| EQ-VAS                                             | X (X – X)                  | X (X – X)                     | X                        | X – X                   |         |

† at 6 months

**Figure 4.** Between group change in overall 90-day symptomatic VTE rate and non-inferiority margin. The dotted line represents the non-inferiority margin

[figure not shown]

**Table 4.** Outcomes for populations 2, 3 and 4

| Population                                                                          | Outcome                                            | LMWH
Allocation
(n = X) | Aspirin
Allocation
(n = X) | Absolute Risk
Difference | 95% Confidence
Interval | p-value |
|-------------------------------------------------------------------------------------|----------------------------------------------------|-------------------------------|----------------------------------|-----------------------------|----------------------------|---------|
| All primary THA/TKA for any diagnosis eligible to receive study drug (population 2) | Any Venous thromboembolism                  | n (%)                         | n (%)                            | X                           | X – X                      |         |
|                                                                                     | Type of Venous thromboembolism              |                               |                                  |                             |                            |         |
|                                                                                     | Pulmonary embolism                                 | n (%)                         | n (%)                            | X                           | X – X                      |         |
|                                                                                     | Deep venous thrombosis                             | n (%)                         | n (%)                            | X                           | X – X                      |         |
|                                                                                     | Both Pulmonary embolism and deep venous thrombosis | n (%)                         | n (%)                            | X                           | X – X                      |         |
|                                                                                     | Above knee deep venous thrombosis                  | n (%)                         | n (%)                            | X                           | X – X                      |         |
|                                                                                     | Below knee deep venous thrombosis                  | n (%)                         | n (%)                            | X                           | X – X                      |         |
|                                                                                     | Death                                              | n (%)                         | n (%)                            | X                           | X – X                      |         |
|                                                                                     | Re-operation (90d)                                 | n (%)                         | n (%)                            | X                           | X – X                      |         |
|                                                                                     | Reoperation (6 months)                             | n (%)                         | n (%)                            | X                           | X – X                      |         |
|                                                                                     | Re-admission                                       | n (%)                         | n (%)                            | X                           | X – X                      |         |
|                                                                                     | Major Bleeding                                     | n (%)                         | n (%)                            | X                           | X – X                      |         |
|                                                                                     | Pain and Function (median and IQR) †    |                               |                                  |                             |                            |         |
|                                                                                     | Oxford Hip Score                                   |                               |                                  | X                           | X – X                      |         |
|                                                                                     | Oxford Knee Score                                  | X (X – X)                     | X (X – X)                        | X                           | X – X                      |         |
| All HA/KA eligible to receive study drug (population 3)                             | Any Venous thromboembolism                  | n (%)                         | n (%)                            | X                           | X – X                      |         |
|                                                                                     | Type of Venous thromboembolism              |                               |                                  |                             |                            |         |
|                                                                                     | Pulmonary embolism                                 | n (%)                         | n (%)                            | X                           | X – X                      |         |
|                                                                                     | Deep venous thrombosis                             | n (%)                         | n (%)                            | X                           | X – X                      |         |
|                                                                                     | Both Pulmonary embolism and deep venous thrombosis | n (%)                         | n (%)                            | X                           | X – X                      |         |
|                                                                                     | Above knee deep venous thrombosis                  | n (%)                         | n (%)                            | X                           | X – X                      |         |
|                                                                                     | Below knee deep venous thrombosis                  | n (%)                         | n (%)                            | X                           | X – X                      |         |
|                                                                                     | Death                                              | n (%)                         | n (%)                            | X                           | X – X                      |         |
|                                                                                     | Re-operation (90d)                                 | n (%)                         | n (%)                            | X                           | X – X                      |         |
|                                                                                     | Reoperation (6 months)                             | n (%)                         | n (%)                            | X                           | X – X                      |         |
|                                                                                     | Re-admission                                       | n (%)                         | n (%)                            | X                           | X – X                      |         |
|                                                                                     | Major Bleeding                                     | n (%)                         | n (%)                            | X                           | X – X                      |         |
|                                                                                     | Pain and Function (median and IQR) †    |                               |                                  |                             |                            |         |
|                                                                                     | Oxford Hip Score                                   |                               |                                  | X                           | X – X                      |         |
|                                                                                     | Oxford Knee Score                                  | X (X – X)                     | X (X – X)                        | X                           | X – X                      |         |
| All HA/KA including study drug exclusion (population 4)                             | Any Venous thromboembolism                  | n (%)                         | n (%)                            | X                           | X – X                      |         |
|                                                                                     | Type of Venous thromboembolism              |                               |                                  |                             |                            |         |
|                                                                                     | Pulmonary embolism                                 | n (%)                         | n (%)                            | X                           | X – X                      |         |
|                                                                                     | Deep venous thrombosis                             | n (%)                         | n (%)                            | X                           | X – X                      |         |
|                                                                                     | Both Pulmonary embolism and deep venous thrombosis | n (%)                         | n (%)                            | X                           | X – X                      |         |
|                                                                                     | Above knee deep venous thrombosis                  | n (%)                         | n (%)                            | X                           | X – X                      |         |
|                                                                                     | Below knee deep venous thrombosis                  | n (%)                         | n (%)                            | X                           | X – X                      |         |
|                                                                                     | Death                                              | n (%)                         | n (%)                            | X                           | X – X                      |         |
|                                                                                     | Re-operation (90d)                                 | n (%)                         | n (%)                            | X                           | X – X                      |         |
|                                                                                     | Reoperation (6 months)                             | n (%)                         | n (%)                            | X                           | X – X                      |         |
|                                                                                     | Re-admission                                       | n (%)                         | n (%)                            | X                           | X – X                      |         |
|                                                                                     | Major Bleeding                                     | n (%)                         | n (%)                            | X                           | X – X                      |         |
|                                                                                     | Pain and Function (median and IQR) †    |                               |                                  |                             |                            |         |
|                                                                                     | Oxford Hip Score                                   |                               |                                  | X                           | X – X                      |         |
|                                                                                     | Oxford Knee Score                                  | X (X – X)                     | X (X – X)                        | X                           | X – X                      |         |

† at 6 months

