### 3.8. Participant timeline

| Time Point    | Data Collection Questions and Instruments                                                                                                                                                                                                                                                                                                      |
|---------------|------------------------------------------------------------------------------------------------------------------------------------------------------------------------------------------------------------------------------------------------------------------------------------------------------------------------------------------------|
| Pre-operative | Current anticoagulation use (yes/no and drug)
History of previous VTE
Age
Sex
Joint (hip or knee)
Side
Unilateral vs bilateral
Primary or revision
ASA grade
BMI
Oxford Hip or Knee Score
EQ-5D-5L
EQVAS
Low back pain
Joint pain (numeric rating scale 0-10)
Expectations (pain and improvement) |
| 90 days       | VTE (DVT or PE)
Adherence (did you use pills or injections to prevent a blood clot post-operatively, for how long?)
Current use of anticoagulants (yes/no, which one)
Complications (asked individually, as per complication list)                                                                                                    |
| 6 months      | Complications (asked individually, as per complication list)
Oxford Hip or Knee Score
EQ-5D-5L
Joint pain (scale 0-10)
Satisfaction with outcome of surgery
Patient-rated improvement                                                                                                                                           |

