### **Outcome variables**

The primary outcome of the study is symptomatic VTE within 90 days of surgery. Secondary outcomes are:

- Deep vein thrombosis (DVT) only (total, below-knee and above-knee) within 90 days
- Pulmonary embolism (PE) only within 90 days
- Readmission related to the original surgery or associated treatment (including bleeding and VTE-related) within 90 days
- Reoperation on the same joint within 90 days and within 6 months of surgery
- Major bleeding events within 90 days defined as bleeding events resulting in readmission, reoperation or death
- Death within 90 days
- Change in patient-reported pain, function and health status measures as measured by the Oxford Hip Score (OHS), Oxford Knee Score (OKS), EQ-5D score and the EQ-VAS from baseline to 6 months postoperatively

Outcome and demographic data were collected preoperatively (demographics, patient reported pain, function and health status) and at 90 days and 6 months postoperatively. Data for all primary and secondary outcomes are patient-reported (except for death). All patients who responded 'yes' to having experienced a VTE or a secondary operation within 6 months had this result verified by AOANJRR staff through contact with treating doctors and hospitals. A random audit of 200 patients who did not report a VTE event was undertaken to detect the false negative reporting rate. All data collected for registered patients specific to CRISTAL have been outlined in the published protocol [15]. Mortality data were collected through linkage between the AOANJRR and the National Death Index.

In the published protocol [15], mortality was to be measured at 90 days and 6 months. Due to the lack of sensitivity in measuring VTE-related mortality at 6 months, and due to the lag in data availability for mortality, we will only analyse mortality at 90 days [17].

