### ***Methods used for Interim Analyses***

Interim analyses were conducted for VTE and mortality within 90 days for population 1. To account for unequal cluster sizes, incomplete crossover or clusters which had not yet crossed over, a composite analysis was designed. For clusters which had crossed over, including with partial completion of the second period, the cluster weighted estimator intended for the primary outcome was used. Harmonic mean weighting when there are unequal cluster sizes has been shown to improve precision and 95% confidence interval coverage compared with unweighted or inverse variance estimates [25, 26]. Clusters which had not crossed over were analysed using the cluster period summaries, weighted by cluster size, in a parallel design approach, i.e., as if it were a cluster randomised trial without crossover. Estimates for the two approaches were combined using inverse variance weights to provide a final estimate. Confidence intervals were constructed using the Haybittle-Peto boundary of 0.001.

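### The Oxford, EQ-5D and EQ-VAS outcomes are defined as change but analysed and tabulated as 6-month scores, without adjusting for the pre-operative score; adjustment is a modest free gain in precision

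*Supplement*

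**What the plan says.** The final SAP describes these outcomes in three ways.

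- Outcome variables lists "Change in patient-reported pain, function and health status measures", measured from baseline to 6 months.
- Main analyses says that "for continuous outcomes such as pain score, the cluster mean will be the mean outcome", and states that effects on the secondary outcomes will be given as absolute risk differences.
- Table 3 has a block headed "Pain and Function (median and IQR", footnoted as 6-month values, beside a risk-difference column with a 95% interval.

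On the model, Main analyses says: "In a linear regression of cluster differences on treatment sequence, the treatment effect estimate is the intercept". Sequence is the only regressor. Hospitals that never reached their second period are handled separately: "Clusters which had not crossed over were analysed using the cluster period summaries, weighted by cluster size, in a parallel design approach" (Methods used for Interim Analyses). This carries over, since "final analyses of the primary and secondary outcomes will use the same composite method as the interim analyses" (Main analyses).

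The final protocol, section 3.8, lists among the pre-operative items "Oxford Hip or Knee Score EQ-5D-5L EQVAS Low back pain", and SAP Table 2 displays the baseline scores. Apart from defining change, baseline scores have two other uses: as auxiliary variables for multiple imputation (SAP, Methods for handling missing data), and for adjustment in a cost-effectiveness analysis that is done only if aspirin proves inferior (protocol section 3.15).

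**The concern.** There are two linked problems.

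First, the estimand is not fixed. Two analysts could follow this SAP and report different estimates, one of mean change and one of the mean 6-month score. A risk difference is not a possible effect measure for either.

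Second, neither reading uses the baseline score as a covariate. Each hospital's two arms are different patients in consecutive periods, so their pre-operative scores can differ. The sequence term removes a period effect that is common to all hospitals. It does not remove a shift in case mix peculiar to one hospital, or differences between hospitals in the clusters that did not cross over. Both add noise that a measured covariate could reduce. At stake are intervals for the secondary outcomes that are somewhat wider than they need be, and estimates that carry whatever baseline imbalance chance produces.

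**Working it through.** **The plan's own figure.** The SAP sizes the trial on VTE only: 2.5% against 1.5%, one-sided 0.025, 90% power, intracluster correlation (ICC) 0.01, interperiod correlation (IPC) 0.008, 31 hospitals.

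- Individual randomisation, pooled-variance formula for two proportions: 4,117 per group.
- Patients per arm per hospital: m = n(1 − ICC)/(K − n(ICC − IPC)) = 4,117 × 0.99/(31 − 4,117 × 0.002) = 179.03, rounded up to 180.
- Total: 2 × 31 × 180 = 11,160.

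All three agree with the SAP. It gives no standard deviation, correlation or power for the patient-reported scores.

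**Per-patient variance.** Let r be the correlation between baseline and 6-month score, with equal SDs set to 1. The variance is 1 for the raw 6-month score, 2(1 − r) for change and 1 − r² after baseline adjustment. For every r strictly between 0 and 1 the last is the smallest. The documents give no r; I assume 0.3 to 0.5.

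- r = 0.3: 1, 1.4 and 0.91.
- r = 0.5: 1, 1.0 and 0.75.

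**Standard error in this design.** The estimator works on cluster-period means, so a cluster-period component remains. If baseline explains patient-level variance only,

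SE = √{2[(ICC − IPC) + v(1 − ICC)/m]/K},

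where v is the per-patient variance above. With m = 180 and ICC = 0.01, (1 − ICC)/m = 0.0055; K = 31. For example, the raw score with ICC − IPC = 0.002 gives √{2(0.002 + 0.0055)/31} = 0.0220. In SD units:

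| ICC − IPC | r | raw | change | adjusted | cut vs raw | cut vs change |
|---|---|---|---|---|---|---|
| 0.002 | 0.3 | 0.0220 | 0.0250 | 0.0213 | 3.4% | 15.0% |
| 0.002 | 0.5 | 0.0220 | 0.0220 | 0.0199 | 9.6% | 9.6% |
| 0.01 | 0.3 | 0.0316 | 0.0338 | 0.0311 | 1.6% | 7.9% |
| 0.01 | 0.5 | 0.0316 | 0.0316 | 0.0302 | 4.5% | 4.5% |

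The value 0.002 is borrowed from VTE; 0.01 is a less favourable assumption. With 100 patients per arm per hospital and 0.002, the cut against the raw score is 3.8% to 11.0%.

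**Imbalance.** If the arms differ at baseline by d SD, the raw estimate shifts by r·d and the change estimate by −(1 − r)·d. With d = 0.1 and r = 0.3 these are +0.03 and −0.07 SD. Adjustment removes both in expectation. Chance alone gives d a standard deviation of about √{2/(31 × 180)} = 0.019 over the whole trial, so the typical shift is small.

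**Bias.** In 3,000 simulated trials per setting (31 hospitals, two periods, 180 per cell, randomised sequence) the raw, change and adjusted estimates all averaged zero to within 0.001 SD. The difference between them was in spread.

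**The case against.** The strongest reply is that the planned analysis is valid: randomised sequence protects it, the sequence term deals with a common period effect, and adjustment is only a matter of efficiency. That stands. It is also fair that the mean outcome in Main analyses could be read as mean change, that medians and quartiles may be descriptive only, and that the risk-difference heading is shared with mostly binary rows. This makes the text ambiguous rather than plainly wrong. It does not supply a baseline-adjusted analysis, and the 6-month footnote still pulls against the definition as change.

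A reader might infer more than the documents support:

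- **Bias from case mix.** Sites are unblinded, learn their arm before registration begins, and register patients pre-operatively, so differential registration is possible. Nothing in the documents shows that it occurred.
- **A large loss of precision.** Per-patient ratios look bigger: over r = 0.2 to 0.5 the change score has 33–67% more variance than the adjusted one, 2/(1 + r) − 1, and the raw score 4–33% more, 1/(1 − r²) − 1. They leave out the cluster-period component and so overstate the effect here.
- **A much larger gain if hospitals' periods differ at baseline.** With an assumed 0.2 SD shift and r = 0.5, the simulated SE is 0.034 raw against 0.020 adjusted. But such a shift alone adds 0.5² × 0.2² = 0.01 to the cluster-period variance, five times the 0.002 used beside it, and the documents give no support for it.
- **A baseline score for every patient.** Collection is planned for all, but the SAP's missing-data section names pre-operative pain and function scores as an example of large missing blocks.

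**Conclusion.** The point holds as one of specification and efficiency. The SAP should settle whether it analyses change or the 6-month score, stop calling the contrast a risk difference, and use the baseline scores it collects.

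At assumed r of 0.3 to 0.5, with 31 hospitals, 180 per arm in each and ICC − IPC of 0.002, adjustment cuts the standard error by about 3–10% against the raw 6-month score and about 10–15% against change. If ICC − IPC is 0.01, the cut against the raw score is about 2–5%. These figures assume complete crossover at the planned size. Early stopping makes the actual cell sizes and the share of hospitals without crossover uncertain. The correlations for these scores may also differ from those for VTE.

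The harm is extra variance and chance imbalance, not demonstrated bias. It touches secondary outcomes only; the primary VTE conclusion does not depend on it.

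**What to change.** Amend the SAP before database lock, which its Blinding section allows:

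1. Name the 6-month score as the analysed outcome for each of the four measures, in Outcome variables, Main analyses and the results tables alike.
2. For each measure, regress the 6-month score on its own baseline score at patient level, without treatment in the model.
3. Put the cluster-period means of the residuals into the existing composite estimator, for both the crossover and the parallel parts.
4. Handle missing baseline scores within the SAP's imputation. If chained equations are dropped, as the SAP allows for bounded scores, impute the mean for the baseline covariate.
5. Report an adjusted mean difference with its 95% interval instead of a risk difference. Medians and quartiles can stay as description by arm.

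The cost is a few sentences of SAP text and a few lines of code. No new data are needed and the main estimator is unchanged.
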